**Follow-ups only**			
	Intervention Satisfaction Questionnaire	Acceptability	Satisfaction with intervention
	Recovery plan and safety plan recall	Mechanism	Accuracy of recall

^a^MINI: Mini International Neuropsychiatric Interview.

bDSM-V: Diagnostic and Statistical Manual of Mental Disorders Fifth Edition.

^c^CSSR-S: Columbia Suicide Severity Rating Scale.

^d^EMA: ecological momentary assessment.

^e^BPRS-24: Brief Psychiatric Rating Scale–24 item.

#### Suicidal Ideation Severity and Behavior (Primary Outcome)

We administer the interview-rated version of the *Scale for Suicide Ideation*, a 21-item widely used measure that predicts completed suicide [41,42] in addition to the interval CSSR-S, which queries the timing, severity, and characteristics of suicidal ideation and behavior [30].

Our study addresses changes in suicidal ideation and is underpowered to detect the impact on the risk of suicidal behaviors. Our rationale for change in suicidal ideation as our primary outcome was that for a suicide-specific intervention to be potentially effective, it must be feasible, acceptable, and associated with significant and sustained reductions in suicidal ideation to move on to a confirmatory trial. If the target of suicidal ideation was not moved, then we would not proceed to a confirmatory trial. We recognize that people may experience a reduction in suicidal ideation severity as part of natural regression to baseline. However, we note that people with SMIs are more likely to have chronic ideation than people without psychosis and therefore would be less likely to experience natural reductions in ideation [43]. Moreover, people with SMIs are more likely to have recurrent suicidal ideation, and as such, we added follow-up assessments at 12 and 24 weeks. Finally, we used the minimally important clinical difference of 0.5 SD as a threshold for meaningful reduction and power analyses. We will investigate whether the SSI score is skewed or kurtotic using the convention of +3 investigate skew and, if evident, will dichotomize the variable.

#### Outpatient and Crisis Service Utilization (Secondary Outcome)

We extracted electronic medical record (EMR) encounter data regarding attendance at the first follow-up appointment and rate of follow-up outpatient contacts. It is possible that participants may use out-of-county institutions not captured in the EMR; therefore, the *Cornell Service Use Index* [44] is administered for service use not recorded in the EMR to facilitate a comparison of augmented and nonaugmented arms.

#### Global Psychopathology (Secondary Outcome)

Global psychopathologic severity is evaluated using the *Brief Psychiatric Rating Scale–24-item expanded version 4.0* (BPRS-24) [45], a clinician-rated measure with 24 items that cover depression, anxiety, mania, suicidality, delusions or hallucinations, and unusual behavior.

#### Medication Adherence (Secondary Outcome)

Self-reported adherence is assessed with the *Tablet Routine Questionnaire* [46], which asks about the proportion of psychotropic medication taken over the past week and month.

#### Electronic Adherence and Targets (Secondary Outcome)

A wealth of EMA data will be generated, including adherence data (eg, response rate=the number of responses/number of queries) and patterns of adherence over time. In our completed trial, treatment response was associated with greater adherence; thus, we will also explore this association. We structured the EMA protocol to provide day-to-day data on the early warning signs or triggers, symptoms, medication use, socialization, and contextual influences. These data will inform hypotheses about determinants or contexts of suicidal thoughts in SMIs [47].

#### Substance Use Frequency or Intensity (Moderator)

We assessed substance abuse as an exploratory moderator of attrition, adherence, and response. To quantify alcohol and drug use, we selected the 30-day *Timeline Followback Scale* [48].

#### Therapeutic Mechanisms Variables

We examined mechanistic targets for the START intervention that map on to therapeutic content: *Treatment Engagement*, *Coping Self-Efficacy (CSE) Scale* [49] and *Beck Hopelessness Scale* [50].

#### Safety and Recovery Plan Recall (4, 12, and 24 weeks only)

Modeled after recent research on recall of elements of CBT for bipolar disorder [51] and our research in schizophrenia [15], we administer a knowledge or recall measure that corresponds to elements in the safety plan generated in Session 1 as well as the recovery plan in Session 4. Participants are asked to recall broad elements discussed (eg, responding to early warning signs) and the individual responses of their own plan once prompted (eg, specific responses to early warning signs). Participants’ written responses are coded as fully accurate, partially accurate, or not accurate in regard to recalled elements of the safety and recovery plans.

#### Acceptability Measures

At baseline, participants are administered the *Treatment Rationale Scale* [52], a 3-item self-report that garners perceived credibility and anticipated benefit. Participants also completed seven 5-point Likert-type and 4 open-ended questions (modified from Kimhy et al [53] and used in our prior research [54]) focused on greater intervention satisfaction, barriers and suggestions concerning the intervention, the therapist, and the manual, and for the mobile health condition, experiences with the device and suggestions for future usability.

#### Fidelity

We systematically address the relevant components of treatment integrity: *Competence, Therapist and Participant Adherence, and Treatment Differentiation* [55]. *Competence* is addressed by initial training of the study therapists who meet minimum competence standards (see above) and in an ongoing fashion by audiotape-rated delivery of the intervention, supported by weekly supervision. *Therapist Fidelity* to the manualized protocol is assessed via 100% of session recordings rated by the therapist and research team on an adapted version of the Cognitive Therapy Rating Scale for Psychosis (CTS-Psy) [56]. *Participant adherence* is assessed by session attendance or telephone contacts and objectively via device-obtained data. *Treatment differentiation* is assessed by blinded random selection of 25% of audio-taped sessions rated by masked raters, with a running quarterly calculation of discrepancies between conditions evaluated to determine if content delivered varies between the 2 conditions; retraining occurs if differences in CTS-Psy scores are >0.5 SD.

#### Sample Size Determination

Our pilot trial’s sample size is derived based on the nexus of 3 goals, guided by work on optimization of pilot studies [57]: (1) to obtain point estimates of feasibility, acceptability, and test the impact of the intervention compared with population base rates for engagement and crisis service utilization; (2) to be powered to test a clinically significant within-subjects reduction (*d*>0.5) in the SSI score; and (3) to evaluate the preliminary impact of augmentation. Intent-to-treat analyses with 70 patients, with an alpha of .05, will have 95% power to evaluate whether the sample estimates differ from population estimates (eg, 50% no-show rates) [58] and 77% power for each of the individual arms. On the basis of the General Linear Multivariate Model Power and Sample Size program [59], there is >0.80 power across 24 weeks to detect a 0.5 SD pre-post change in SSI score. We have considerably less power to detect augmentation effects, but following recent research on sample size estimation in pilot trials and confidence intervals [60,61], the preliminary impact of augmentation will be assessed by defining a minimally clinically significant augmentative effect for a future trial.

#### Analysis of Feasibility and Acceptability

Point estimates of feasibility and acceptability included the following: (1) triage clients screened, (2) screened clients eligible, (3) eligible clients enrolled, (4) enrolled clients completing 4 sessions and follow-up calls, and (5) percentage of participants reporting being somewhat or very satisfied with the overall intervention. Comparative data regarding feasibility and acceptability are our completed trials, which enable us to examine whether indicators of feasibility in the triage setting are similar to general outpatient populations. Each of these estimates, in addition to Treatment Rationale and Satisfaction scores, will be contrasted across conditions with *t* tests or Mann-Whitney tests or chi-square tests.

#### Analysis of Within-Person Changes

Distributions for the SSI score may be skewed (with overdispersion due to persons with no present ideation) and, if so, zero-inflated negative binomial models will be employed. We will use hierarchical linear models (HLMs) in which time will be tested as a categorical time-varying predictor of SSI score and subjects are a random effect, with significant reduction in SSI over time indicated by a statistically significant time effect. We expect that by the 24-week time-point, SSI will have at least a medium effect size decrease (*d*≥0.5) as measured by HLM linear-estimated change. To evaluate augmentation, we will examine group×time interactions, with estimated standardized differences considered supportive of the augmentation inclusive of minimal clinical significance CI>0.80. We will evaluate secondary continuous outcomes (eg, BPRS) variables in the same way.

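### The criterion for judging mobile augmentation (CI>0.80) does not say what 0.80 is, and its possible readings give opposite verdicts on the same data

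*Protocol article*

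**What the plan says.** Four sections of the protocol article bear on how augmentation is judged.

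- Analysis of Within-Person Changes: for augmentation, "we will examine group×time interactions", with standardized differences "considered supportive of the augmentation inclusive of minimal clinical significance CI>0.80". Secondary continuous outcomes are to be handled in the same way.
- Suicidal Ideation Severity and Behavior (Primary Outcome): "we used the minimally important clinical difference of 0.5 SD as a threshold for meaningful reduction and power analyses". The reduction meant is the change in SSI within participants.
- Sample Size Determination: power for augmentation is said to be considerably lower, with no figure. Its preliminary impact will be assessed "by defining a minimally clinically significant augmentative effect for a future trial", with no number given. The section cites work on pilot trials and confidence intervals.
- Randomization, Masking, and Trial Design Considerations: if no difference between arms is detectable in feasibility, acceptability, mediators or outcomes while ideation shows sustained improvement, augmentation may not be worth carrying forward. The between-arm comparisons are called secondary.

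**The concern.** The article states a quantitative rule for the between-arm comparison, and the rule cannot be applied as written. The figure 0.80 could be a size the estimate must exceed, a size that a confidence limit must exceed or reach, or the confidence level of an interval that is then compared with zero or with a minimal effect. The neighbouring sections do not choose among these. One gives 0.5 SD, but for within-person reduction. One promises a minimal augmentative effect without a value. One adds a separate rule based on detectability.

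If the readings agreed on most data this would be a matter of wording. If they disagree near 0.5 SD, the size the plan itself treats as meaningful, the verdict depends on an interpretation that could be made after the results are known. The same criterion carries over to the secondary continuous outcomes.

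**Working it through.** **Inputs.** From Sample Size Determination: "Intent-to-treat analyses with 70 patients, with an alpha of .05". The documents do not give the allocation ratio, the correlation rho between baseline and follow-up SSI, or attrition. I assume 1:1 allocation (35 per arm), rho of 0.3, 0.5 and 0.7, no attrition (20% loss, 28 per arm, as a sensitivity case), equal SD at all visits, compound symmetry, standardization by the baseline SD, two-sided intervals and a normal approximation.

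**The plan's own figures.** The article says "there is >0.80 power across 24 weeks to detect a 0.5 SD pre-post change in SSI score". A two-sided paired t-test with n = 70 and d_z = 0.5/√(2(1−rho)) has power 0.831, 0.936, 0.985 and above 0.99 at rho 0, 0.3, 0.5 and 0.7. The statement reproduces, but it concerns within-person change only. The figure of "77% power for each of the individual arms" fits about 35 per arm: an exact one-sided binomial test of 0.70 against 0.50 (both the 0.70 and the one-sidedness are my assumptions) gives 0.952 at n = 70 and 0.773 at n = 35.

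**Standard error of the week-24 group-by-time contrast, baseline means free.** SE = √(2(1−rho)) × √(2/35), and √(2/35) = 0.239.

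- rho 0.3: 1.183 × 0.239 = 0.283
- rho 0.5: 1.000 × 0.239 = 0.239
- rho 0.7: 0.775 × 0.239 = 0.185

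**An observed 0.5 SD at rho 0.5.** The half-widths are 1.96 × 0.239 = 0.469 (95%) and 1.282 × 0.239 = 0.306 (80%). The intervals are 0.03 to 0.97 and 0.19 to 0.81.

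**Readings compared (rho 0.5).** If c is the smallest estimate that counts as supportive and δ is the true effect, P(supportive) = 1 − Φ((c − δ)/SE).

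| Reading | c | Observed 0.5 SD | P at δ = 0.5 | P at δ = 0 |
|---|---|---|---|---|
| 95% lower limit above 0.80 | 0.80 + 0.469 = 1.27 | fails | 0.1% | about 0 |
| Estimate above 0.80 | 0.80 | fails | 10.5% | about 0 |
| 95% interval reaches 0.80 | 0.80 − 0.469 = 0.33 | passes | 76% | 8% |
| 80% interval lies above 0 | 0.31 | passes | 79% | 10% |
| 80% upper limit reaches 0.5 | 0.50 − 0.306 = 0.19 | passes | 90% | 21% |

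If the last reading also requires the lower limit not to exceed 0.5, so that the interval strictly contains 0.5, then P at δ = 0.5 is 80% by construction.

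**Sensitivity.** Over rho 0.3 to 0.7 and 28 to 35 per arm, c is 1.16 to 1.42 for the 95% lower limit above 0.80, 0.18 to 0.44 for a 95% interval reaching 0.80, and 0.24 to 0.41 for an 80% interval above 0. An observed 0.5 SD fails the first and passes the other two throughout.

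**The detectability rule.** If detectable means significant at two-sided 5%, power at a true 0.5 SD is 0.55 (rho 0.5). For SSI, that rule would often miss an effect of this size.

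**Use of baseline.** With a common baseline mean, or baseline SSI as covariate, the variance factor is 1 − rho² instead of 2(1−rho). The ratio is (1+rho)/2 = 0.65, 0.75 and 0.85 at rho 0.3, 0.5 and 0.7. At rho 0.5 the SE falls from 0.239 to 0.207, and two-sided 5% power at 0.5 SD rises from 0.55 to 0.68.

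**A workable rule, for illustration.** Take an 80% interval with half-width h and a minimal effect of 0.5 SD. Call the result not supportive if the upper limit is below 0.5; otherwise supportive if the lower limit is above 0; otherwise inconclusive. Without baseline adjustment h is 0.362, 0.306 and 0.237 at rho 0.3, 0.5 and 0.7. The chance that the lower limit exceeds 0 at a true 0.5 SD is 69%, 79% and 92%. The order of the categories matters only where 2h < 0.5, here at rho 0.7 (2 × 0.237 = 0.474). There, supportive needs an estimate of at least 0.5 − 0.237 = 0.263, and the 92% becomes 1 − Φ((0.263 − 0.5)/0.185) = 90%. At a true zero effect, supportive is called 10%, 10% and 1 − Φ(0.263/0.185) = 8% of the time.

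**The case against.** The strongest reply is that 0.80 is probably a confidence level. Sample Size Determination appeals to work on confidence intervals in pilot trials, and an 80% interval would fit that. On this reading nothing clashes with 0.5 SD, which is in any case stated for within-person reduction; a separate between-arm minimum is not a contradiction. This stands. A reader might infer that the article contradicts itself on the minimal difference, but that follows only if 0.80 is an effect size. The reply does not rescue the rule, however. An 80% interval must still be compared with something, and comparison with 0 or with an unnumbered minimum gives different thresholds (0.31 or 0.19 in the table) and different rates of support under no effect (10% or 21%).

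A reader might also infer that the planned interaction wastes the baseline measurement. The article does not support that. Baseline SSI is one of the repeated assessments, the text does not say whether baseline means are free or constrained, and a model with a common baseline mean recovers the full gain. An analysis plan may settle this, and likewise the visit for the contrast; the preceding sentence already names week 24 for within-person change.

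A strict reading of the 80% interval would refuse support to an observed 0.9 SD, because its interval of 0.59 to 1.21 excludes 0.5. An analyst is unlikely to apply the rule that mechanically, and the point does not depend on it.

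Finally, an article condenses a fuller document, and this comparison is secondary in a pilot. The first part excuses omissions, but here a criterion is stated and cannot be used. The second limits the consequence.

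**Conclusion.** The point holds as a defect in a stated decision rule. At an observed 0.5 SD the plausible readings return opposite verdicts, and at a true 0.5 SD the chance of support ranges from about 0.1% to 90%. The probabilities assume 35 per arm, no attrition, rho 0.5 and a contrast with free baseline means; the split in verdicts persists over rho 0.3 to 0.7 and with 20% loss.

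The tension with 0.5 SD is conditional on 0.80 being an effect size. The handling of baseline is an opportunity for more precision and not an error.

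It would go too far to say that the trial's main conclusion is open to choice after the data are seen. The primary success criterion is aggregate change in SSI, and the decision against augmentation also weighs feasibility, acceptability and mediators. What is exposed is the SSI part of the decision on carrying augmentation forward, together with the secondary continuous outcomes judged the same way.

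**What to change.** Reconcile the four sections into one rule for the week-24 between-arm SSI difference in baseline-SD units:

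1. State the confidence level, for example a two-sided 80% interval.
2. State the minimal between-arm effect, for example 0.5 SD or another value that the sponsor justifies, and say that it is distinct from the within-person threshold if that is intended.
3. Use mutually exclusive verdicts in a fixed order: not supportive if the upper limit is below the minimal effect; otherwise supportive if the lower limit is above 0; otherwise inconclusive.
4. Say how this rule relates to the detectability rule in Randomization, Masking, and Trial Design Considerations.
5. Report the rule's operating characteristics over a range of correlations, as in the working above.

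As a free improvement, estimate the contrast with a common baseline mean or with baseline SSI as a covariate. Against an unconstrained interaction this cuts the variance by 35%, 25% and 15% at rho 0.3, 0.5 and 0.7.

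The cost is wording and one model term, with no new data. The article reports recruitment as still active, so the rule could be settled before results are known.

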#### Analysis of Mechanisms

For analysis of binary mechanisms (outpatient engagement) and outcomes (crisis service use), we will use chi-square analyses to examine associations at 24 weeks. For the continuous time-varying mechanism (CSE), we will examine a mechanistic association between changes in CSE and SSI scores using the Macarthur framework [61]. We will use generalized estimating equations to evaluate the prediction of crisis service use by within-subjects change in CSE and then repeat these analyses within mobile-augmented and nonaugmented arms. We will also contrast the Safety or Recovery Plan recall at weeks 4, 12, and 24 using *t* tests or Mann-Whitney U tests.

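### The 24-week engagement–crisis chi-square ignores time order, and the CSE–crisis model is repeated within each arm with no arm × CSE-change term

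*Protocol article*

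**What the plan says.** In the Protocol article, Analysis of Mechanisms, outpatient engagement is the binary mechanism and crisis service use the binary outcome. For these, "we will use chi-square analyses to examine associations at 24 weeks". No window, lag or ordering of the two variables is given.

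For coping self-efficacy, described there as continuous and time-varying, "we will examine a mechanistic association between changes in CSE and SSI scores using the Macarthur framework". Generalized estimating equations (GEE) then predict crisis service use from within-subject change in CSE, "and then repeat these analyses within mobile-augmented and nonaugmented arms". No term for arm by change in CSE is mentioned. Plan recall is handled separately: "We will also contrast the Safety or Recovery Plan recall at weeks 4, 12, and 24".

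Other sections bear on this:

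- **Safety Procedures:** an increase in ideation or new suicidal behavior sets off urgent evaluation, linkage to resources, provider notification and hospitalization arrangements.
- **Outpatient and Crisis Service Utilization:** first follow-up attendance and later outpatient contacts come from medical-record encounter data.
- **Analysis of Within-Person Changes:** augmentation on continuous outcomes is examined by group × time interaction.
- **Randomization, Masking, and Trial Design Considerations:** arm comparisons are secondary and preliminary, and mediators are among the dimensions on which the arms will be compared.

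**The concern.** A mechanism has to act before the outcome it explains. A table of ever engaged against ever in crisis over 24 weeks pools three kinds of participant: those whose crisis followed engagement, those whose crisis led to linkage, and those whose crisis kept them from intake. Only the first kind says anything about engagement as a mechanism. The other two can create an association in either direction. If crises prompt linkage, engagement looks harmful; if crises prevent intake, engagement looks protective, which is the result a reader would hope for.

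The within-arm repeats raise a separate problem. Two fits, one per arm, each show whether CSE change relates to crisis use in that arm. They do not show whether the relation differs between arms. A reader who sees a significant result in one arm and not in the other will be inclined to conclude that the mobile component changes how START works, and that conclusion needs an estimate of the difference itself.

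**Working it through.** **Inputs from the protocol.** Sample Size Determination gives 70 participants and an alpha of .05. There are two arms; no allocation ratio is stated, so 35 per arm is inferred. The protocol gives no crisis rate, no effect of a crisis on engagement and no CSE–outcome correlation. All values for these below are assumptions.

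**The plan's own figure.** No power is given for any mechanism analysis. The nearest statement is "Intent-to-treat analyses with 70 patients, with an alpha of .05, will have 95% power" for a comparison with a population rate such as 50%, with 77% for each arm. An exact one-sided binomial test against 50% with a true rate of 70% gives 95.2% at n = 70 and 77.3% at n = 35. This agrees with 35 per arm, but the 70% and the one-sided alpha are back-solved, not stated. The two-sided exact test gives 92.2% and 65.2%.

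**Step 1: chi-square without time order.** Suppose engagement has no effect on crises, base engagement is 50%, and a crisis raises later engagement to 75%. With a 20% crisis rate, the expected table for 70 people is:

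| | Engaged | Not engaged | Total |
|---|---|---|---|
| Crisis | 10.5 | 3.5 | 14 |
| No crisis | 28 | 28 | 56 |
| Total | 38.5 | 31.5 | 70 |

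Crisis risk appears as 10.5/38.5 = 27% in the engaged and 3.5/31.5 = 11% in the others, though engagement does nothing. The chi-square at these expected counts is 70 × (10.5 × 28 − 3.5 × 28)² / (14 × 56 × 38.5 × 31.5) = 2,689,120 / 950,796 = 2.83, so z = 1.68. The chance of exceeding 1.96 is about Φ(1.68 − 1.96) = 0.39. Simulation of such tables (100,000 per scenario) gives the same value and the range below: share of trials significant, with the continuity-corrected test in brackets.

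| Engagement after a crisis | Crisis rate 10% | 20% | 30% |
|---|---|---|---|
| 50% (no link) | 5% (1%) | 5% (2%) | 5% (3%) |
| 60% | 7% (3%) | 10% (5%) | 12% (7%) |
| 65% | 11% (4%) | 17% (10%) | 21% (14%) |
| 75% | 22% (10%) | 39% (27%) | 50% (38%) |

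The scenario lets every crisis precede and alter engagement, so it is an upper bound for a given shift. By symmetry around 50%, a fall in engagement after a crisis gives the same rates with the opposite sign.

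**Step 2: within-arm repeats.** As a simple stand-in for the GEE, take a CSE–outcome correlation r that is the same in both arms. Power in an arm of 35, by Fisher's z, is approximately Φ(atanh(r) × √32 − 1.96). The chance that exactly one arm is significant is 2p(1 − p), with p that power.

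| r in both arms | Power per arm, p | Exactly one arm significant |
|---|---|---|
| 0.2 | 21% | 33% |
| 0.3 | 42% | 49% |
| 0.4 | 67% | 44% |
| 0.5 | 87% | 22% |

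For r = 0.3: 2 × 0.417 × 0.583 = 0.486. Every one of these split results would be chance, because the true relation is identical.

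**Step 3: what a direct test can do.** The standard error of the difference between two Fisher z values is √(2/32) = 0.25. For r = 0 in one arm against 0.3, 0.4, 0.5 or 0.6 in the other, power is Φ(atanh(r)/0.25 − 1.96) = 24%, 40%, 59% and 79%. The interaction answers the right question but is weak at this size. Events are few as well: at crisis rates of 10%, 20% and 30%, an arm of 35 has 3.5, 7 and 10.5 participants with an event.

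**The case against.** The strongest objection is that the chi-square may be meant by arm: each binary variable compared between the randomized groups. The service-use section says the data are to support a comparison of the arms, and the model section covers only continuous secondary outcomes. On that reading randomization supplies the time order and the reverse-path argument falls. The ambiguity is real. But the sentence stands under mechanisms and pairs a mechanism with an outcome, so engagement by crisis is the more natural reading. If the other is meant, no engagement–crisis mechanism test is described at all.

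Second, a reader might infer that all the mechanism analyses fail, or that the CSE–SSI analysis lacks time order. The document does not support this. CSE is treated as time-varying under a named mediator framework whose lag structure a condensed article may leave to the full plan, and recall is contrasted at three visits.

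Third, a reader might infer that the protocol judges arm differences by comparing the within-arm results. It does not say so; it says only that the analyses are repeated, and elsewhere it uses interactions. What stands is that the repeats alone cannot show a difference.

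Fourth, the false-positive rates rest on chosen inputs. Participants enter with an outpatient appointment pending, so many crises may follow first attendance, and the rates fall with smaller shifts, rarer crises or a continuity correction. This limits the size of the problem, not its existence.

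Finally, the trial is a pilot that admits limited power between arms and for suicidal behavior, and progression rests on feasibility, acceptability and reduced ideation. That keeps the consequence modest.

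**Conclusion.** The point holds for two stated analyses. First, on the natural reading, the 24-week chi-square counts crises that precede and alter engagement as evidence about engagement, and Safety Procedures describes such a path. Its false-positive rate is about 10–20% for a shift in engagement from 50% to 60–65%, and about 40–50% for a shift to 75%, uncorrected and at assumed crisis rates of 20–30%. Second, repeating the CSE–crisis model by arm does not test whether the relation differs. With an inferred 35 per arm and assumed equal correlations of 0.2–0.5, split significance arises in roughly 20–50% of trials.

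The existence of both problems follows from the stated methods; only their size depends on the assumptions. The stake is the interpretation of how START works and what the mobile component adds, not the main decision to proceed. The change is worth making because it is cheap.

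**What to change.** In Analysis of Mechanisms:

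1. State whether the chi-square relates engagement to crisis use or compares each of them between arms. If the latter, say that no engagement–crisis mechanism test is planned, or add an ordered one.
2. If engagement is to be related to crises, use the encounter data already extracted to put engagement first: either a landmark analysis (engagement by a fixed week against crises after it) or engagement as a time-varying exposure.
3. Replace the within-arm repeats, or accompany them, with one pooled GEE for crisis use containing arm, CSE change and arm × CSE change. Report the interaction as an estimate with its confidence interval, not as a significance verdict.
4. Label both analyses exploratory.

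This changes wording and analysis only; no new data are needed, provided the extracted encounters and the crises carry dates. The costs are statistical. A landmark drops crises before the cut-off from an already small number of events; a time-varying exposure keeps more of them but needs dates for both. The interaction will have a wide interval at this sample size, and the report should say so.
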